**Organization**

***Clinical centers.*** Each of the 22 participating clinical centers have a Principal Investigator and additional staff to carry out the protocol that may include recruitment coordinators, dieticians, physicians, nurses, data collectors, and others. Moreover, each has an internal or external local Biochemistry Laboratory where the intermediate Group B biochemical measurements are performed. Finally, each clinical unit is associated with a Metabolic Fitness center, where all patients perform fitness assessment and strength and flexibility evaluation and EXE patients also the prescribed exercise program, supervised by at least one Metabolic Fitness instructor.

***Coordinating center.*** The Coordinating Center is at the Diabetology Unit of the Sant’Andrea Hospital, the teaching hospital of the II School of Medicine & Surgery of the University of Rome “La Sapienza”. It is responsible for biostatistical design, analysis, and data storage and processing. The Unit of Clinical Pathology of the same institution serves as central laboratory for baseline and final biochemical measurements.

***Steering committee.*** The Steering Committee is the representative body of the IDES Research Group. It is composed of the Study Coordinator and experts of the various aspects involved in the research (see Appendix 3).

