# **Treatments**

***Exercise program***

The training program for the EXE group consists of twice a week supervised sessions of 75 min duration of mixed (aerobic and resistance) exercise, for 12 months.

Aerobic training will be performed using treadmill, step, elliptical, arm or cycle-ergometer. Transformation of maximal oxygen consumption (VO2max)in exercise load will be performed by the use of a software (Wellness System, Technogym SPA, Gambettola, Italy) or a dedicated spreadsheet, which allow calculation of the individual training load for each equipment from VO2max using the American College of Sports Medicine (ACSM) equations [21].

Resistance training will consist of 4 resistance exercises, i.e. thrust movement on the transverse plane (chest press or equivalent), traction movement on the frontal plane (lateral pull down or equivalent), squat movement (leg press or equivalent), trunk flexion for the abdominals, and three stretching positions. Intensity will be adjusted according to improvements in predicted VO2max and 1RM, as recorded throughout the study, thus resulting in further increments of working loads. In addition, caloric expenditure will be increased progressively by 0.1 kcal/kg body weight/session every month (Table 5).

Subjects in the EXE group will be allocated to either moderate-intensity aerobic (at 55% of predicted VO2max) and resistance (at 60% of predicted 1 Repetition Maximum, RM) or high-intensity aerobic (at 70 % of predicted VO2max) and resistance (at 80% of predicted 1RM) exercise, depending on the centres, which have been preliminary assigned to exercise patients at moderate- or high-intensity. Exercise and duration of aerobic training and number of series will be managed to obtain the same caloric expenditure per kg body weight, independent of the intensity level of exercise.

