**Statistical analysis**

***Sample size calculation***

Sample size calculation will be based on the mean HbA1c values (7.6±1.6 %) detected in the SFIDA population, consisting of 11,000 type 2 diabetic patients, aged 46-69 years, a HbA1c reduction of at least 0.5 % in EXE vs. CON group and a statistical power of 90% (α=0.05). To this end, 215 patients per arm need to be enrolled (430 patients total). Assuming a dropout rate of up to 25%, we will recruit 600 patients. Such a sample size also guarantees a statistical power of >90% to detect changes indicated for each of the parameters in the secondary endpoints.

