***Statistical analysis plan***

The c2 test for categorical variables and the Student’s t test or the corresponding nonparametric Mann-Whitney test for continuous variables will be utilized to compare patients’ characteristics at baseline. The efficacy of intervention on primary and secondary endpoints will be assessed using the unpaired t-test or the Mann Whitney U test for continuous variables, by comparing between-groups changes from baseline to end-of-study. For categorical variables (i.e. medications), logistic regression analysis will be applied, with end-of-study rate of use included in the model as the dependent variable and baseline rate of use and study arm included as covariates.

To account for change in medication throughout the 12-month period, multiple regression analysis will be performed, with baseline-to-end-of-study changes as dependent variable and treatment at baseline and treatment initiation during the study as dichotomous variables (yes versus no), whereas drug dosage will not be taken into consideration.

Within group end-of-study vs. baseline values will be compared using the McNemar test for categorical variables and the Wilcoxon signed ranks test for continuous variables. To identify independent predictors of HbA1c changes from baseline, a multiple regression analysis was applied, with mean value of METs, baseline HbA1c values, gender, age, and changes in HOMA-IR, BMI, waist, total, LDL-cholesterol and HDL-cholesterol, and hs-CRP as covariates forced in the model.

Multivariate analysis techniques (multiple or logistic regression) will be used to adjust for differences in the distribution of one or more parameters between the two arms, whereas the ANOVA trend test will be applied for evaluating the relationship of volume and intensity of exercise training (dose/response) and fitness variation with modifiable cardiovascular risk factors.

The likelihood to achieve glycaemic and nonglycaemic targets after 12 months will be estimated using logistic regression, adjusted for baseline status (on-target vs. not-on-target).

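### The primary test has no centre term, although centre is a randomisation stratum and supervised exercise is given by centre in EXE only, so its standard error can err in either direction

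*Protocol*

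**What the plan says.** - **Delivery.** Each of the 22 clinical units is tied to a fitness centre. Both arms are assessed there, and there "EXE patients also the prescribed exercise program, supervised by at least one Metabolic Fitness instructor" (Protocol, Organization, Clinical centers).
- **Intensity.** EXE patients train at moderate or high intensity "depending on the centres, which have been preliminary assigned to exercise patients at moderate- or high-intensity" (Exercise program).
- **Randomisation.** Patients are randomised individually in permuted blocks, stratified by centre and, within centre, by age and type of diabetes treatment (Type of randomization).
- **Sample size.** It rests on "mean HbA1c values (7.6±1.6 %) detected in the SFIDA population", "a HbA1c reduction of at least 0.5 % in EXE vs. CON group" and "a statistical power of 90% (α=0.05"), which gives "215 patients per arm need to be enrolled (430 patients total"). Then: "Assuming a dropout rate of up to 25%, we will recruit 600 patients" (Sample size calculation). No ICC or design effect appears.
- **Primary test.** Efficacy on the primary and secondary endpoints "will be assessed using the unpaired t-test or the Mann Whitney U test for continuous variables", applied to changes from baseline (Statistical analysis plan). The regressions in that section cover medication change, predictors of HbA1c change, arm imbalances and target attainment. None names a centre or instructor term.

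**The concern.** Two features of the design make patients of one centre alike, and the named test reflects neither.

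First, both arms of a centre share its clinic staff, counselling, diet prescription and drug adjustment. Stratified randomisation balances this between arms. A test that ignores the stratum leaves the between-centre variance in its standard error, which is then too large.

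Second, EXE patients of a centre also share a gym, one or more instructors and an intensity level. CON has no counterpart, so stratification cannot balance this part. If the training effect differs between centres, the test's standard error is too small for an average effect meant to apply beyond these centres.

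At stake are the true error rate and interval width of the primary comparison, and the meaning of the stated 90% power. The protocol itself names the test, so the point is not merely left to a later analysis plan.

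**Working it through.** **1. The plan's own figure.** Difference 0.5, SD 1.6, power 90%, α = 0.05. Sidedness is not stated; two-sided reproduces the result.

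n per arm = 2 × (1.6/0.5)² × (1.960 + 1.282)² = 215.2, so 216 when rounded up, against 215 stated. One-sided would give 176. The stated number is thus the plain two-sample result, with no allowance for clustering. Dropout: 430/0.75 = 573.3, so 574, rounded up to 600. That leaves 600 × 0.75 = 450 completers, 225 per arm, or 225/22 = 10.2 per arm per centre.

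**2. True variance against the t-test's variance.** Let ρs be the share of variance due to a centre effect common to both arms, ρe the share due to an EXE-only centre effect, and m the patients per arm per centre. With 1:1 allocation within centre the shared effect cancels from the difference, so

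R = true variance / t-test variance ≈ 1 − ρs + (m − 1)ρe/2

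and the type I error of the t-test is 2 × [1 − Φ(1.96/√R)]. With m = 10, and ρs and ρe assumed because the document gives neither:

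| Shared ICC | EXE-only ICC | R | Type I error |
|---|---|---|---|
| 0 | 0 | 1.000 | 5.0% |
| 0.05 | 0 | 0.950 | 4.4% |
| 0.10 | 0 | 0.900 | 3.9% |
| 0.10 | 0.02 | 0.990 | 4.9% |
| 0 | 0.02 | 1.090 | 6.0% |
| 0.05 | 0.05 | 1.175 | 7.1% |
| 0 | 0.05 | 1.225 | 7.7% |

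Simulation with 22 centres and 10 patients per arm per centre agrees with rows two to seven to within about 0.3 percentage points. The two errors cancel when ρs = (10 − 1)/2 × ρe, that is, when the shared ICC is 4.5 times the EXE-only ICC.

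**3. Power with EXE-only variation.** For 225 completers per arm and SD 1.6, the EXE design effect is DE = 1 + (10.23 − 1)ρe and SE = 1.6 × √[(1 + DE)/225]. Large-sample power is Φ(0.5/SE − 1.96). A test of a random centre-by-arm term has about 21 degrees of freedom, with critical value 2.080 instead of 1.960.

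| EXE-only ICC | DE | SE | Power, large-sample | Power, about 21 df |
|---|---|---|---|---|
| 0 | 1.00 | 0.151 | 91% | 89% |
| 0.01 | 1.09 | 0.154 | 90% | 88% |
| 0.02 | 1.18 | 0.158 | 89% | 86% |
| 0.05 | 1.46 | 0.167 | 85% | 81% |

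The last column is about what Φ(0.5/SE − 2.080) gives; the noncentral t distribution is up to 1 point lower.

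**4. Interval width.** The change of critical value alone costs 2.080/1.960 = 1.06, so 6% even at ICC zero. With the SE ratio included, the interval is 1.045 × 1.061 = 1.11 times as wide at ICC 0.02, and 1.109 × 1.061 = 1.18 times at 0.05.

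**5. What the assumed ICCs mean.** An EXE-only ICC of 0.02 is a between-centre SD of the training effect of 1.6 × √0.02 = 0.23 HbA1c points, around an assumed mean of 0.5. An ICC of 0.05 is 1.6 × √0.05 = 0.36 points.

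**The case against.** The strongest reply is that a reader might infer that the standard errors are too small and the power overstated. The document does not support that. It gives no ICC, no number of instructors and no caseload. CON patients attend the same clinics, and the shared effect pulls the other way: a shared ICC of 0.10 with an EXE-only ICC of 0.02 puts the t-test at 4.9%. This stands, and it is why the point is worded in both directions.

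Four further arguments:

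- **An unusual null.** If training works nowhere, it creates no EXE-only variance. Inflation needs effects of opposite sign that average to zero, with the centres regarded as a sample of possible centres. For the average effect in these 22 centres only, simulation gives about 5% at ICC 0.05 and 4% at 0.10. This stands for type I error. It does not settle interval width when the true effect is not zero, and the stated aim concerns type 2 diabetic subjects with the metabolic syndrome, with no limit to these sites.
- **Standardised delivery.** Calorie targets are fixed by month (Table 5) and energy expenditure per kg is the same at both intensities. This may well keep the EXE-only variation small, but it cannot be shown from the document.
- **The SD matters more.** The 1.6 describes HbA1c values, whereas the test uses change. At an assumed baseline-to-final correlation of 0.6, the SD of change is 1.6 × √(2 × 0.4) = 1.43 and large-sample power at ICC 0.05 is about 92%; at 0.4 the SD is 1.6 × √(2 × 0.6) = 1.75 and power about 78%. This stands as a caution on every power figure here.
- **Low stakes at small ICC.** At 0.01, rounding up to 600 absorbs the loss on the large-sample reckoning (90%). This also stands.

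**Conclusion.** The point holds in conditional form. The named primary test ignores a stratum that the trial randomises on and a treatment delivered by centre in one arm only, so its actual error rate is not known to be 5%. Under the assumed ICCs the type I error runs from about 4% (shared effect only) to about 8% (EXE-only ICC 0.05, no shared effect), and the two errors can cancel. The 90% power is correct arithmetic under independence. With EXE-only variation at ICC 0.02 or 0.05 it would be about 89% or 85% (large-sample), or about 86% or 81% on about 21 degrees of freedom. These figures rest on equal centre sizes, an SD of 1.6 for change, and 25% dropout spread evenly over arms and centres. The document fixes neither the sign nor the size of the error, and nothing here shows that the trial is too small.

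**What to change.** 1. **Statistical analysis plan section.** Make the primary analysis of change in HbA1c a linear model with arm and centre. This removes the shared centre variance from the standard error. It also removes the accidental offset to any EXE-only variation, so the second step belongs with it.
2. **Same section.** Pre-state a sensitivity analysis that adds a random centre-by-arm (EXE-only) term with small-sample degrees of freedom. Whether that term should be in the primary model is debatable, since it depends on whether the target is these 22 centres or centres in general.
3. **Sample size calculation.** State that the 90% power assumes no EXE-only centre variation. If a range is shown, give it for 225 completers per arm and SD 1.6, label the ICCs as assumptions, and say whether the degrees-of-freedom correction is included.

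**Cost.** Only wording changes; centre is already needed for the randomisation, and enrolment stays at 600. The sensitivity interval is somewhat wider: about 6% at ICC zero, and about 11% or 18% at an EXE-only ICC of 0.02 or 0.05, relative to the plain t-test with no centre variation.

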**Week Number Day of the Week Activity code Activity Duration Notes**

[figure not shown]

**Table 1:** Inclusion and exclusion criteria.

**Inclusion criteria**

1. Type 2 diabetic patients with Metabolic Syndrome, according to IDF criteria
2. Diabetes duration >1 year.
3. Age 40-75 years at screening
4. BMI 27- 40 kg/m2
5. Sedentary for at least 6 months*.
6. They must have been treated by prescribed diet and/or OHA e insulin
7. Able to walk for long distances unaided.
8. Eligible after positive outcome of cardiac evaluation .

* Sedentary patients were defined: (1) those expending less than 10% of their leisure time expenditure in activities involving > 4 MET; (2) those who did not practice any leisure time physical activity and who also were above the median in the number of hours spent sitting down during leisure time.

**Exclusion criteria**

1. All patients with a history of central nervous dysfunction such as hemiparesis, myelopathies, cerebral ataxia, significant musculoskeletal deformities such as an amputation, dysmetria, or scoliosis, patients with movement abnormalities or arthritis limited by pain when exercising.
2. A history of clinical evidence of severe cardiovascular disease which may limit or be a contraindication for exercise.
3. Clinical evidence of vestibular dysfunction
4. Angina and related symptoms
5. Postural hypotension defined as a fall in arterial blood pressure when changing position of >20 mmHg (systole) or >10 mmHg (diastole)
6. History of plantar sores.

**Table 2:** Recruitment and follow-up process

| **Phase** | **Visit** | **Action** |
| --- | --- | --- |
| **Recruitment** | **R1** | Registration of eligible patients in the IDES database together with their demographic, anthropometric and clinical data  Participation acceptance and informed consent sign  Prescription of ophthalmologist and cardiologist consultation for retinopathy and CVD evaluation |
| **R2** | Return of ophthalmologist and cardiologist evaluation  Administration of the SF-36 and the WHO-DTSQ questionnaires  Administration of the Minnesota LTPA questionnaire  Structured individualized counseling intervention  Collection of blood and urine samples for baseline, Group A biochemical measurements and forwarding to the central laboratory via express courier  Appointment at the Metabolic Fitness Center for metabolic fitness assessment and strength evaluation  Communication of the group assignment  Information about the exercise program (EXE group) |
| **R3** | Registration of results of baseline, group A biochemical measurements  Registration of data from Minnesota LTPA questionnaire  Nutritional evaluation and prescription of a treatment regimen according to the current guidelines, including diet prescription  Consignment of a diary for prospective assessment of physical activity  Prescription for intermediate, group B biochemical measurements |
| **Follow-up** | **F1** | Intermediate anthropometric and blood pressure measurements  Registration of results of intermediate, group B biochemical measurements (with eventual treatment regimen modification)  Registration of data from the diary of physical activity  Structured individualized counseling reinforcement  Prescription for intermediate, group B biochemical measurements |
| **F2** | Intermediate anthropometric and blood pressure measurements  Registration of results of intermediate, group B biochemical measurements (with eventual treatment regimen modification)  Registration of data from the diary of physical activity  Structured individualized counseling reinforcement  Prescription for intermediate, group B biochemical measurements |
| **F3** | Intermediate anthropometric and blood pressure measurements  Registration of results of intermediate, group B biochemical measurements (with eventual treatment regimen modification)  Registration of data from the diary of physical activity  Structured individualized counseling reinforcement |
| **F4** | Final anthropometric and blood pressure measurements  Collection of blood and urine samples for baseline, Group A biochemical measurements and forwarding to the central laboratory via express courier  Registration of data from the diary of physical activity  Administration of the SF-36 and the WHO-DTSQ questionnaires  Appointment at the Metabolic Fitness Center for metabolic fitness assessment and strength evaluation |

**Table 3:** Biochemical measurements

***Group A*** – to be performed at central laboratory (Laboratory of Clinical Chemistry, Sant’Andrea Hospital, Rome, Italy) at baseline and at the end of the study.

- HbA1c a, blood glucose b, C-peptide, and insulin levels c with calculation of the Homeostasis Model Assessment-Insulin Resistance (HOMA-IR) index from fasting glucose and insulin levels using the HOMA Calculator© software ([www.dtu.ox.ac.uk/homa/index.php](http://www.dtu.ox.ac.uk/homa/index.php));
- serum triglycerides and total and HDL-cholesterol levels b with LDL-cholesterol calculation using the formula: total cholesterol – [HDL-cholesterol + (triglycerides/5)];
- BUN, uric acid and serum creatinine b, with calculation of estimated glomerular filtration rate (eGFR) is calculated from serum creatinine by the modified Modification of Diet in Renal Disease Study Group equation ([www.kidney.org/professionals/KDOQI/gfr_calculator.cfm](http://www.kidney.org/professionals/KDOQI/gfr_calculator.cfm)), and urinary albumin d / creatinine b ratio in spot urine sample (these data are presented elsewhere);
- serum aspartate aminotransferase, alanine aminotransferase, -glutamyl-transpeptidase and creatine phosphokinase levels b;
- hs-C reactive protein b.

a High-performance liquid chromatography (Adams TMA1C HA-8160, Menarini Diagnostics, Florence, Italy).

b VITROS 5,1 FS Chemistry System (Ortho-Clinical Diagnostics, Inc, Raritan, NJ, USA)

c Chemiluminiscent immunometric assays (Immulite 2000 Thes; Diagnostic Products Corporation, Los Angeles, CA, USA)

dmAlb VITROS (Ortho-Clinical Diagnostics, Inc)

***Group B***– to be performed in each centre laboratory at 3, 6 an 9 months.

- HbA1c and blood glucose levels;
- serum triglycerides and total and HDL cholesterol levels with LDL cholesterol calculation;
- BUN, serum creatinine, urinalysis, uric acid (if present hypeuricemia);
- serum aspartate aminotransferase, alanine aminotransferase, -glutamyl-transpeptidase and creatine phosphokinase levels (if treated with statins);
- plasma sodium and potassium levels (if treated with BP-lowering agents).

**Table 4:** List of Physical Activities (in Italian) and the relative METs intensities utilized to predict the accumulated volume of physical activity (METs·h-1·wk-1). Activities included and corresponding METS values are derived from the Minnesota Leisure Time Physical Activity Questionnaire.

| **PHYSICAL ACTIVITY** | **METS** |
| --- | --- |

1 Passeggiare 3.5

2 Camminare da casa al lavoro o nella pausa lavoro 4.0

3 Camminare (portando un carrello con la spesa) 3.5

4 Camminare (portando le sporte della spesa) 5.5

5 Salire le scale 8.0

6 Camminare in campagna/traking 6.07

7 Escursioni con lo zaino 7.0

8 Scalate in montagna 8.0

9 Andare in bicicletta al lavoro 4.0

10 Ballo 4.5

11 Aerobica o balletto 6.0

12 Giocare con i bambini 4.5

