# On the third visit (R3), basal anthropometric and blood pressure (BP) measurements will be obtained and registered in the database, together with results of laboratory tests performed centrally. Subsequently all patients will receive a treatment regimen aimed at achieving optimal glycemic, lipid, BP and body weight targets, as established by current guidelines. This program will eventually include glucose-, lipid- and BP-lowering agents as needed and, when indicated, anti-platelet drugs. For ethical reasons, drugs will be also adjusted throughout the study to attain target levels and to account for reduced needs. The treatment regimen will include also a dietary prescription, which will be preceded by a preliminary nutritional evaluation with assessment of BMI and the individual patient requirements and preferences. The diet will contain 55% calories from complex carbohydrates, 30% from fat, and 15% from protein. Since all patients are overweight or obese, they will receive a low calorie diet (negative balance of 500 kcal/day, not <1500 Kcal in males and 1200 Kcal in females), calculated by adding the estimated energy expenditure from non-conditioning or non-volunteer and conditioning or volunteer physical activity to basal metabolism estimated using the gas exchange analyzer FitMate (Cosmed, Rome, Italy). Baseline LTPA will be calculated by multiplying the weekly hours spent in the various activities, as reported in the Minnesota LTPA questionnaire, by the metabolic equivalent (MET) score of each activity, and expressed as METs· h–1 · week–1. Patients will be also given a diary to be filled in daily with type of physical activity performed and time spent in each of them (Figure 2 and Table 4). Finally, patients will receive a list of intermediate, group B biochemical measurements, to be performed at each center laboratory immediately before the next visit (Table 3), will be prescribed.

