***Type of randomization***

Patients will be randomized centrally by the use of a permuted-block randomization computer program, stratifying the enrolled subjects by center and, within each center, by age (<60 vs. ≥60 years) and type of diabetes treatment (diet ± oral agents vs. insulin).

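### Change in HOMA-IR, calculated from measured insulin with no exception for insulin-treated patients, is forced into the HbA1c predictor model without any treatment term

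*Protocol*

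**What the plan says.** **The index.** Table 3, Group A, lists "C-peptide, and insulin levels c with calculation of the Homeostasis Model Assessment-Insulin Resistance (HOMA-IR) index", calculated "from fasting glucose and insulin levels using the HOMA Calculator" software. Group A is assayed centrally "at baseline and at the end of the study", so a change score can be formed. No patient group is excepted. C-peptide is in the same panel but is not an input to the index.

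**Who is enrolled.** Table 1, inclusion criterion 6, reads "They must have been treated by prescribed diet and/or OHA e insulin". The Type of randomization section stratifies within centre by age and by "type of diabetes treatment (diet ± oral agents vs. insulin". Insulin users were therefore expected in sufficient number to stratify on, though no proportion is given.

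**What happens to their drugs.** In the recruitment section, the regimen set at visit R3 is described so: "This program will eventually include glucose-, lipid- and BP-lowering agents as needed". It adds that "drugs will be also adjusted throughout the study to attain target levels and to account for reduced needs". The follow-up section has the regimen modified at visits F1 to F3 where needed, and the changes recorded in the database.

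**How the index is used.** In the Statistical analysis plan section, the regression for predictors of HbA1c change has "changes in HOMA-IR, BMI, waist, total, LDL-cholesterol and HDL-cholesterol, and hs-CRP as covariates forced in the model", together with physical activity volume, baseline HbA1c, sex and age. The list contains no medication term and no study-arm term.

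**The concern.** HOMA-IR is meant to describe resistance to the patient's own insulin. When some of the measured insulin has been injected, the index also responds to the dose. A patient who starts insulin between the two samples can show a higher index with no increase in resistance, while HbA1c falls because of the drug. Insulin treatment is then a common cause of the covariate and the outcome, and the model has nothing to separate the two.

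The visit order makes this more likely. Baseline Group A blood is taken at R2 and the treatment regimen is prescribed at R3. All study-driven drug changes, including the initial optimisation, therefore fall between the two HOMA-IR measurements.

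At stake is the interpretation of one exploratory regression: whether change in insulin resistance independently predicts change in HbA1c. Physical activity volume is in the same model. The protocol also lists reduction in glucose-lowering drugs as a between-arm outcome, so it allows that dosing may differ by arm. An artefact in the HOMA-IR term could therefore carry over to the activity coefficient.

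**Working it through.** **1. The plan's own figures.** The protocol gives no figure for HOMA-IR. Its sample size is not in dispute and reproduces. With SD 1.6, difference 0.5, power 90% and two-sided α = 0.05 (sidedness is assumed), n per arm = 2 × [1.6 × (1.960 + 1.282) / 0.5]² = 215.2, against the stated 215.

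**2. Is there a treatment term in the predictor model?** No. Medication is handled in a separate regression of baseline-to-end changes, with treatment at baseline and treatment initiation as yes/no variables and dose disregarded. Those terms are not in the predictor model's covariate list. Adding them would help only in part, because a dose change in an existing user would still be invisible.

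**3. Size, under assumptions.** The documents do not give the share of patients starting insulin, the resulting shift in the index, or how far the assay detects injected insulin. Let

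- p = share starting insulin between the two samples (assumed 5% to 20%);
- d = the shift this causes in change in HOMA-IR, in within-group SDs (assumed 0.5 to 2);
- b = the accompanying HbA1c change (assumed −0.5 points);
- v = p(1 − p).

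Fraction of the covariate's variance due to drug start: f = v·d² / (1 + v·d²).

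Spurious single-covariate slope, with no true relation present: b·d·v / (1 + v·d²), in HbA1c points per SD.

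| p | d = 0.5 | d = 1 | d = 2 |
| --- | --- | --- | --- |
| 5% | 1.2%; −0.012 | 4.5%; −0.023 | 16.0%; −0.040 |
| 10% | 2.2%; −0.022 | 8.3%; −0.041 | 26.5%; −0.066 |
| 20% | 3.8%; −0.038 | 13.8%; −0.069 | 39.0%; −0.098 |

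Worked cell: p = 10%, d = 1 gives v = 0.09, f = 0.09 / 1.09 = 8.3%, slope = −0.5 × 0.09 / 1.09 = −0.041.

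A true slope β would appear as β(1 − f) plus the spurious term. Across the table, 1 − f runs from 0.99 to 0.61.

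**4. Direction.** The table covers starts only. The protocol also allows reductions to follow reduced needs. In such patients measured insulin falls (shift −d) while HbA1c is stable or better. If HbA1c falls by the same assumed 0.5 points, the sign of d flips and the spurious slope runs from +0.012 to +0.098. If equal shares p start and reduce, the two contributions to the covariance cancel and the spurious slope is zero. The covariate is still noisier: f = 2p·d² / (1 + 2p·d²), for example 0.10 / 1.10 = 9.1% at p = 5%, d = 1. The net sign depends on a mix of starts and reductions that the documents do not give.

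**The case against.** The strongest reply is that this is a small matter of detail. HOMA-IR is neither the primary outcome nor a named secondary outcome. It is one covariate in one descriptive regression, and who contributes to a derived index is often settled in the SAP, which is not at hand. The protocol never says that the index will be analysed in insulin users, and it never names insulin initiation. Both are inferred from the absence of an exception and from the general permission to use glucose-lowering drugs. Medication is not ignored either, since a separate regression addresses it.

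Most of this stands as a limit on importance. It does not remove the point, because the protocol itself fixes both the inputs of the index and the forced covariate list, and following them as written produces the contaminated covariate.

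Three stronger readings are tempting and are not supported:

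- **A reader might infer that every insulin user is affected.** At an assumed 10% to 20% of the 450 patients left after 25% dropout from 600, that would be 45 to 90. The covariate is a change score, however. A user on similar insulin at both samples has the inflation at both times and shows no spurious jump. The number whose insulin changed is unknown.
- **A reader might infer that the index rises in proportion to measured insulin**, for example by 50% if insulin is 1.5 times higher. That holds glucose fixed, although insulin lowers it and glucose also enters the index. Under a simple product index with glucose 20% lower, 1.5 × 0.8 = 1.2, a rise of 20%.
- **A reader might infer that the coefficient takes the wrong sign.** Starts and need-driven reductions push in opposite directions. Even with starts alone, reversal requires a true slope smaller than the spurious one, and the documents give no true slope.

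**Conclusion.** The point holds as a minor one. As written, change in HOMA-IR partly reflects insulin treatment in patients whose insulin was started, raised or reduced between the two samples, and the predictor model cannot tell this from a change in resistance. Its coefficient is confounded, and coefficients of correlated covariates may be as well.

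This rests on two assumptions: that the immunometric assay named in Table 3 detects injected insulin to some degree, and that some patients' insulin treatment does change. The text allows the second but does not quantify it. Neither the size nor the direction of the bias can be determined from the documents, and the figures above are illustrations only.

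The between-arm HbA1c test, the sample size and the listed secondary endpoints do not use HOMA-IR and are not affected.

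**What to change.** State in Table 3, and again beside the predictor model in the Statistical analysis plan section, how insulin-treated patients are handled. There are two options:

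1. **Restriction.** Limit every analysis that uses HOMA-IR to patients not on insulin at baseline or at end of study. This needs no new data, since baseline treatment defines a stratum and therapy changes are recorded. The cost is fewer patients in one exploratory model, whose results then apply only to patients not on insulin.
2. **C-peptide.** Compute the index from fasting glucose and the C-peptide in the same Group A panel, which reflects the patient's own secretion. The documents do not say whether the named software accepts C-peptide, so this must be confirmed first. The cost is that check and a recalculation at both time points.

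If both are feasible, name one as the main version and keep the other as a sensitivity analysis. Neither option alters patient management.
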